### 6.2 Statistical Analysis Plan:

Quantitative data will be analysed using SPSS and presented using percentages, means (SD), modes, medians (IQR) as appropriate.

Qualitative data interviews will be digitally recorded, verbatim transcripts will be prepared from the sound files, transcripts checked for accuracy against the sound files and anonymised. Thematic content analysis will be used to code data in transcripts that is relevant to the process evaluation. NVivo software will be used to assist with the analysis. One researcher trained in qualitative research methods will analyse the qualitative data allowing for fuller immersion and to obtain an overall sense of the data. Initial open coding will be organised into higher level coding, and

thematic interpretations. Data analysis will be iterative such that early interviews can inform questions in later interviews. Quantitative and qualitative data will be integrated to provide an overall perspective on the process of implementing the intervention/study. We will do that by describing what was delivered in the intervention, what process effects were observed, then identify explanatory 'Context + Mechanism → Process effect' alignments that explain how the intervention, and the study more broadly, was perceived by participants, if/why this varied, and how these perceptions affected receptivity to the intervention.

Once data entry is finalized, study data will be assessed for incompatible, discrepant or clinically implausible values. Outlying values for all distributions, in isolation and over time, will be identified. Any concerning data will be reconciled against original source data. Following completion of cleaning the database will be locked.

The study sample will be described in detail. Continuous variables will be described by their means and SDs, medians and IQRs, and their range; while categorical variables will be described by their counts and percentages in each category.

Feasibility outcomes will be similarly described. These include the number of enrolled patients who complete the baseline and follow-up assessments, and the number of patients who partake in all planned activities versus less than all; the number of patients that require medical review and the timeframe to Medical review; changes in muscle strength and mass from baseline to end of programme assessments; changes in dietetic assessments from baseline to end of programme assessments; changes in QOL outcome measures from baseline to end of programme assessments; the number of patients enrolled in the programme; extra Health Care Professional time required and resources required for the intervention; and reasons for not completing the programme will be collected through Drop Out Forms and with qualitative discussions with HCP involved in the programme.

Missing data will be evaluated, and based on what we observe, dealt with in whatever manner we find appropriate based on current best practices. All analyses will be conducted using the R Project for Statistical Computing and the RStudio IDE. All trial reporting will be done following CONSORT and the CONSORT addendum for pilot/feasibility trials [22].

All analyses will be conducted and/or supervised by the HRB CRF-C Principal Statistician ([name]), under their established quality systems and SOPs, and in accordance with *ICH E9 Statistical Principles for Clinical Trials* and *ICH E6 Good Clinical Practices*.

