|                  | 
 
Please see Section 4.1 and 4.2, Inclusion & Exclusion Criteria for full list and description.
 
                                                                                                                                                                                                                                                                                                                                                                                                                                                                                                                                                                                                                                                                                                                                                      |
| Intervention     | 
Men's Cancer Survivorship Programme:
 
A 12-week group-based interventional programme is proposed for men with advanced genitourinary cancers, encompassing intensive multidisciplinary input to provide men with personalised tools and coping mechanisms for life with cancer. The programme is based upon providing a supportive and safe enabling environment for the introduction of self-care interventions using a group-based format supported by individualised counselling according to the participant's identified needs. This will involve an allied health professional-led programme to include physiotherapist input twice per week, dietitian input two-weekly, specialist nursing input weekly, medical social worker input and psycho-oncology input weekly, with programme oversight by medical oncologists, in the Mardyke Arena, University College Cork (UCC).
 |

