### 2.1 Hypothesis

The introduction of a men's malignancy survivorship programme into routine follow up care will be feasible and will result in improved symptom management and quality of life in patients with advanced genitourinary cancers.

Should this intervention prove feasible, we plan to use the data generated from this feasibility study as the basis for a Quality Improvement (QI) initiative for our patients in the future, by offering this programme to all of our patients as a standard component of clinical care.

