### 3.3 Primary Study Endpoint:

The primary endpoint of this study is to determine the feasibility and acceptability of introducing a men's cancer survivorship programme into routine follow up care in patients with advanced genitourinary malignancies.

The programme acceptability will be measured with each participant at programme completion and at the 6-month post intervention timepoint. PPI feedback at quarterly engagement meetings will also contribute to understanding the level of acceptability of and support for the study. To determine feasibility of such a multi-disciplinary project, success is multifactorial, and this will be reviewed by the Steering Committee throughout the project and during the scheduled PPI engagement meetings to inform subsequent phases. Qualitative interviews where participant

feedback is provided and the final analysis by the steering and research groups in conjunction with key stakeholders will all contribute to the final determination of the feasibility of the programme. This will help explore what elements of the intervention worked, what elements did not work, and what elements require improvement. A purposefully designed brief feasibility questionnaire will be used in line with previously developed questionnaires by our team [7]. This will be created as part of the scoping review.

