#### 4.4.3 Survivorship Programme Procedures

The survivorship programme is a 12-week group-based interventional programme for men with advanced cancer, encompassing intensive multidisciplinary input to provide men with personalised tools and coping mechanisms for life with cancer. The programme is based upon providing a supportive and safe enabling environment for the introduction of self-care interventions using a group-based format supported by individualised counselling according to the participant's identified needs. This will involve an allied health professional-led programme to include physiotherapist input twice per week, dietitian input every 2 weeks, specialist nursing input every 2 weeks, medical social worker input and psycho-oncology input, with programme oversight by medical oncologists, in the Mardyke Arena, UCC. An outline of the programme is provided in the 12-week intervention programme (Section 4.3.2) and Study Calendar (Section 5.0).

Research and relevant Clinical Staff will be trained in the protocol. Following successful completion of the Ethics Committee approved informed consent process, a unique study identifier will be applied to all subject's study data

and will be used exclusively as a unique identifier in study Case Report Forms. Subject's clinical notes will be reviewed, and an appointment arranged for the baseline visit.

The initial visit in the Mardyke Arena, UCC will assess and manage current symptomatology and needs per management pathways, refer to appropriate specialists, and ensure future access to the clinic where needed during the study period. Patients will receive education, exercise, diet and symptom management plan, depending on the outcome of the baseline assessments, or according to clinical judgement. The baseline physical and nutritional assessments will be undertaken at this visit. Diet education and personalised nutrition counselling will be performed throughout the study (For further information see Nutritional Intervention section 4.4.3.2).

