#### 4.4.4 Instruments for data collection

##### Dose and Reach

The time taken to deliver the intervention will be collected (dose). Level of engagement with the interventions will be scored on a Likert scale (one item on the usability scale). Reach relates to the proportion of the intended population participating, demographic details of participants will be collected and shared anonymously. Targeted recruitment will be used to encourage participation of a demographically heterogeneous sample.

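### The only attendance summary the protocol names, all activities versus less than all, cannot separate good from poor attendance, and no stated result would mean not feasible

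*Protocol*

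**What the plan says.** Section 3.3 makes feasibility and acceptability the primary endpoint. It states that "success is multifactorial, and this will be reviewed by the Steering Committee throughout the project", and that interviews and a final analysis by the steering and research groups with stakeholders "will all contribute to the final determination of the feasibility of the programme". Section 6.2 adds "Feasibility outcomes will be similarly described", meaning by counts, percentages, means and medians. Its list includes completed assessments, numbers enrolled, staff time, drop-out reasons, changes in strength, diet and quality of life, and, for attendance, "the number of patients who partake in all planned activities versus less than all".

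The Dose and Reach paragraph of Section 4.4.4 records the time taken to deliver the intervention, and says "Level of engagement with the interventions will be scored on a Likert scale (one item on the usability scale").

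Section 2.1 states what follows from a positive verdict: "Should this intervention prove feasible, we plan to use the data generated from this feasibility study as the basis for a Quality Improvement" initiative, in which the programme is offered to all patients as standard care.

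The content of the programme is described differently in different places:
- Nursing: "specialist nursing input weekly" in the synopsis, but "specialist nursing input every 2 weeks" in Section 4.4.3 and two-weekly in Section 4.3.2. The Section 5.0 Schedule marks weeks 3, 5, 7, 9 and 11 as available on request.
- Dietetics: weeks 2, 4, 8 and 10 in the provisional schedule of Section 4.3.2, but weeks 2, 4, 6, 8 and 10 in the Section 5.0 Schedule.
- Psychological coaching is optional (Section 4.3.2).
- Virtual or recorded catch-up is only to be explored (Section 4.4.3).
- A replacement may join a group already under way (Section 4.4.7.1).

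**The concern.** The trial has one primary question, whether the programme is feasible, and the answer supports offering it to all patients. Two features weaken that answer.

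First, no level of recruitment, retention, attendance or acceptability is stated at which the programme would be judged not feasible. The only stopping provision is the safety pause in Section 7.1, which concerns adverse events. A criterion chosen after the results are known carries little weight.

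Second, the attendance summary treats a man who misses one visit like a man who misses twenty. A man who joins late may be unable to reach the top class however well he attends. Because the set of planned activities is not fixed, two analysts could classify the same man differently.

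**Working it through.** **The plan's own figure.** Section 6.1 sets 60 men to see at least once a process failure that occurs 5% of the time, with 95% confidence. n = ln(1 - 0.95)/ln(1 - 0.05) = 58.4, rounded up to 59, which agrees with the stated 60. The chance of seeing such a failure is 1 - 0.95^60 = 95.4% with 60 men and 1 - 0.95^72 = 97.5% with 72. Going from 60 to 72 allows attrition of 1 - 60/72 = 16.7%. The sample size is therefore sound for its purpose. That purpose is to notice a problem, not to judge a rate against a limit.

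**Inputs for the attendance check.** Visits per man: 2 per week x 12 weeks = 24 (Sections 4.3 and 4.4.3.1). Men: 72. The per-visit attendance p and the within-man correlation rho are assumptions; the documents give neither.

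**Independent misses.** Share attending all 24 = p^24.

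| p | share attending all 24 | men of 72 |
|---|---|---|
| 0.95 | 29.2% | 21.0 |
| 0.90 | 8.0% | 5.7 |
| 0.80 | 0.5% | 0.3 |

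For half the men to attend everything, p must be 0.5^(1/24) = 97.2%.

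**Misses clustered within men.** Each man's attendance probability is given a beta distribution with a = p(1 - rho)/rho and b = (1 - p)(1 - rho)/rho, so that visits follow a beta-binomial. The last column is an illustrative graded measure, the share attending at least 18 of 24 visits.

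| p | rho | share attending all 24 | men of 72 | share attending at least 18 of 24 |
|---|---|---|---|---|
| 0.95 | 0 | 29.2% | 21.0 | 99.99% |
| 0.90 | 0.1 | 28.8% | 20.8 | 91% |
| 0.85 | 0.2 | 27.7% | 20.0 | 80% |
| 0.80 | 0.3 | 27.6% | 19.9 | 71% |

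The split returns 20 or 21 men in every row, while true attendance runs over 15 percentage points. The graded measure falls from nearly all men to 71%, and mean attendance would show p directly.

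**A narrower reading of planned activities.** If one activity per week is counted, the share is p^12: 54% at 0.95, 28% at 0.90 and 7% at 0.80. The classification thus depends heavily on a definition that the protocol does not give.

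**Late joiners.** Section 4.4.7.1 allows replacement after a withdrawal in the first 4 weeks. A man who starts in week 5 is offered 24 - 2 x 4 = 16 visits, so against a fixed 24 he cannot exceed 16/24 = 67%. The denominator has to run from each man's own start.

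**The case against.** The strongest defence is that this is a descriptive, mixed-methods process evaluation in which a rounded judgement by several parties is the stated method, and that an unseen analysis plan may add detail. The first half is fair as to method. It does not remove the need to say in advance what would count against the programme. The second half does not help, because Section 3.3 itself fixes the primary endpoint and how it is decided.

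Several stronger readings are tempting, and the documents do not support them:
- *The split is the only participation measure.* Enrolment, completed assessments, drop-out reasons, reach and an engagement item are also collected, and the list in Section 6.2 is open. The case report forms are separate documents and may hold per-session data. The split is only the sole attendance summary that the protocol names.
- *Nearly every man will fall in the lower class.* No attendance rate is documented. At 95% attendance, 54% attend all 24 if rho is 0.1; at 90%, 29% to 43% do for rho of 0.1 to 0.2.
- *Education sessions push the shares lower still.* Scheduled group education appears to sit within the same 24 visits, so counting it again would count it twice.
- *The nursing schedule conflicts three ways.* The on-request entries follow a two-weekly pattern. The clear mismatch is with the synopsis. Whether an on-request item counts as planned remains unstated.
- *Efficacy results decide feasibility.* Strength, diet and quality-of-life changes are already secondary endpoints in Section 3.4. Their listing in Section 6.2 is a double classification, and nothing makes them decisive.
- *The 60 in Section 6.1 can serve as a retention target.* It is a problem-detection size. If true retention were exactly 60/72, fewer than 60 of 72 men would be retained 42% of the time (binomial).

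**Conclusion.** The point holds in two parts. The weightier one is that the protocol states no level meaning not feasible for its sole primary endpoint, although the verdict underpins roll-out. This rests on the text alone.

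The other is that the attendance split is a poor measure. Over 24 visits it is likely to class most men as attending less than everything unless attendance is very high or misses are concentrated in a few men, and about 28-29% in the top class fits true attendance anywhere from 95% to 80%. Those sizes rest on assumed attendance rates and correlations, on reading all activities as all 24 visits, and on no virtual catch-up being counted. That the split discards the degree of attendance and that its denominator is undefined do not depend on those assumptions.

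The differences over nursing and dietetics must be reconciled before any attendance denominator can be applied. This review takes no view on which schedule is right.

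**What to change.** **Section 6.2.** Replace the split with sessions attended divided by sessions offered, for each man. Count scheduled visits from the man's own start date, leave out optional and on-request items, and report virtual catch-up separately. Give the mean, median, IQR and the share of men at or above a fraction stated in advance, with 95% confidence intervals. State that strength, diet and quality-of-life changes do not enter the feasibility verdict.

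**Section 3.3.** Have the Steering Committee fix go, amend and stop levels before pooled data are seen. They should cover recruitment, retention, attendance and acceptability. Retention, attendance and acceptability should be proportions of men enrolled, so that replacements and a final accrual other than 72 are handled. The amend band should apply to every criterion, so that poor attendance cannot pass because retention was adequate. The sponsor should justify the values and should not borrow the 60 from Section 6.1. Interviews and patient involvement then explain the result.

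**Synopsis and Sections 4.3.2, 4.4.3 and 5.0.** Reconcile the nursing and dietetics schedules.

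The cost is protocol wording and a per-session attendance record, if the case report forms do not already hold one. The downside for the sponsor is that the trial could then report that the programme is not feasible.

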## 7.0 Safety and Adverse Events

---

### 7.1 Recording of Adverse Events

Adverse events (AE) of interest (those deemed potentially related to the intervention) will be recorded and assessed for relationship to the intervention programme throughout the study period. Adverse Events will be documented and graded in accordance with Common Terminology Criteria for Adverse Events (CTCAE) v5.0. Patient reporting of an adverse event to an HCP will trigger recording of the AE, these will not be assessed routinely at every visit due to resources.

Serious Adverse Events (SAE's), defined for the purposes of this study as CTCAE v5.0 grade  $\geq 3$  adverse events of any kind, or those grade  $< 3$  but deemed by an investigator to be serious, will be reported to the LIAM Mc Steering Group for review at the following meeting. SAE's of grade  $\geq 4$  will trigger a pause in the study for safety reasons until the AE has been formally assessed by the Steering Group and a decision made to either proceed with or terminate the study.

We do not anticipate any adverse events associated with completion of the patient reported outcomes. Patients will have the option of skipping questions they do not wish to answer. In event that study participation does result in any event that has significant negative consequences for the subject, this will be recorded by an investigator in the EDC (Electronic Data Capture) and will be reported to the Sponsor and Ethics committee.

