## The LIAM Mc Trial

Review of previous imaging assessing the location, type of, history and progression of bone metastases will be defined at the outset.

Bone pain details at rest, ADL's and with physical activity will be recorded.

Incidence and severity of any adverse event and skeletal complications related to and unrelated to exercise will be recorded throughout the programme.

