##### Survey Questions

The survey will include open-ended questions asking if the participant had any comments about their experience of participating in the intervention/study; elements of the intervention that worked/didn't work and changes they would like to make.

Other process evaluation data will be collected during the study e.g. timing and difficulties experienced with program components, frequency of adverse events (if any), implementation problems. Implementation problems identified during the study will be catalogued as they arise including the mechanisms by which issues are addressed.

Participants will be asked to complete a brief feasibility questionnaire adapted from Zellinger et al (2015) and based on the work of [name] and [name] (both co-applicants) [7], to assess the applicability, acceptability, practicality and relevance of the intervention. The survey will include Likert scale items relating to satisfaction with intervention components.

Qualitative semi structured individual and focus group interviews involving intervention participants and HCPs working within the broader interdisciplinary team will be conducted. The research team including the interventionalists, PPI representatives and key stakeholders (e.g. NCCP representative [name]) will be asked to partake in individual interviews to glean the perspectives of those delivering the intervention and the wider context into which the intervention is delivered.

A semi-structured interview guide will guide an open, in-depth interview with participants about their experience of the trial/intervention, how participants made sense of the intervention, the acceptability of the interventions, their engagement in the processes of the interventions, and the barriers and facilitators encountered.

In addition the interviewer will explore the mechanisms through which the intervention brings about changes which is crucial to understanding both how the effects of the specific intervention occurred and how these effects might be replicated by similar interventions in the future (MRC, 2015).

Context includes anything peripheral to the intervention that may influence its implementation, reach, or its effects. Thus, understanding the context is critical to understanding the potential impact of context on the implementation of the intervention.

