### 6.1 Sample size justification

Parallel Sampling Groups will be used from Q3 of Year 1 on (after completion of the 6 participant Initial Phase). A new group of 6 participants will commence the programme every 6 weeks, in order to facilitate workload and resource management (see Figure 2, Section 3.2.1). This will mean two groups are at two different timepoints in the programme at any given date. 12 groups of 6 men each are planned in total, including the pilot phase group, with a total anticipated accrual of 72 participants over two years.

Given that the main objectives of this study are to evaluate the *feasibility* of introducing a men's malignancy survivorship programme, we have not calculated the sample size that would be required to reliably estimate the effect of the programme on patient outcomes. This follows from established best practices in pilot and feasibility studies [19] for which there is usually too much uncertainty in the various factors that are needed to make a sample size calculation robust (e.g. effect sizes of interest, outcome variability, etc.). Our sample size justification is instead based on trying to recruit the largest possible sample given existing financial and pragmatic constraints. This will allow us to maximize our ability to identify barriers to implementation, as well as the information that will be required to properly design any subsequent trials of the programme's efficacy (e.g. robust estimation of estimator variability, even for binary outcomes [20]). At the same time, the potential costs of over-recruitment are largely absent for this study. Most importantly, there are no excess risks to patients receiving the intervention, and all patients are guaranteed access to the current standard of care. Further, most of the financial costs of the study are fixed, regardless of the actual number of patients recruited into the study.

Given that the goal of a feasibility study is to identify problems that would impede the conduct of a larger, efficacy study, we have set the sample size at 60 based on advice from Viechtbauer et al. [21], which is aimed at being able to detect failures in study processes that would occur just 5% of the time (with 95% confidence). A sample size of 72 allows for sample attrition from men withdrawing, illness, or waning commitment as commented.

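### Sections 4.4.3.1 and 7.1 set different scopes for recording adverse events; if 7.1 governs, the reported event frequency will tend to be too low

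*Protocol*

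**What the plan says.** Section 4.4.3.1, under the safety and tolerability assessment, states: "Incidence and severity of any adverse event and skeletal complications related to and unrelated to exercise will be recorded throughout the programme".

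Section 7.1 states: "Adverse events (AE) of interest (those deemed potentially related to the intervention) will be recorded and assessed for relationship to the intervention programme". On how events come to be recorded, it makes the man's report to a health care professional the trigger and adds that "these will not be assessed routinely at every visit due to resources".

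For serious events Section 7.1 uses a wider scope. Grade 3 and above counts whatever the cause ("adverse events of any kind, or those grade" below 3 that an investigator considers serious), and a serious event of grade 4 or above "will trigger a pause in the study for safety reasons until the AE has been formally assessed by the Steering Group".

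Section 4.4.4 (Survey Questions) lists, as examples of process-evaluation data, "frequency of adverse events (if any), implementation problems". Section 6.1, arguing that recruiting more men carries little cost, says that "there are no excess risks to patients receiving the intervention".

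**The concern.** A site team working from Section 4.4.3.1 and one working from Section 7.1 would build different adverse event datasets. The first logs everything and can sort by cause later. The second discards lower-grade events at the point of entry if nobody thinks them related, and relies mainly on the man mentioning them. A statistical analysis plan cannot repair this, because events that were never recorded cannot be recovered.

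The frequency of adverse events is one output of the process evaluation, and Section 2.1 plans to offer the programme to all patients if it proves feasible. Some of these men have bone metastases and will do progressive resistance and aerobic exercise. A low count that partly reflects how events were collected could be read as evidence of safety, and Section 6.1 already words the absence of excess risk as a fact.

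**Working it through.** **1. The two rules side by side**

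| | Section 4.4.3.1 | Section 7.1 |
|---|---|---|
| Scope below grade 3 | Any event, plus skeletal complications | Events deemed potentially related, or judged serious by an investigator |
| Scope at grade 3 and above | Any event | Any event |
| Relatedness | Not a condition for recording | A condition for recording, and then assessed again |
| How events are found | Not stated | Patient report is the trigger; no routine assessment at every visit |
| Period | The programme | The study period |

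The reference points differ slightly (exercise in one, the whole intervention in the other), but any event is still wider than potentially related events. During the 12 programme weeks, the lower-grade events that 7.1 admits are a subset of those that 4.4.3.1 admits. Section 7.1 runs longer, so the reporting window also needs to be stated.

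**2. Direction of the bias**

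Let p be the true proportion of men with a given event and s the probability that an affected man's event is recorded. The recorded proportion is s × p. Because s cannot exceed 1, the recorded proportion can equal p but cannot exceed it in expectation. The documents give no value for s, so the size of the shortfall cannot be derived.

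**3. The plan's own sample size figure**

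Section 6.1 aims to detect a process failure occurring 5% of the time with 95% confidence:

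- n = ln(1 − 0.95) / ln(1 − 0.05) = 58.4, rounded up to 59. The plan's 60 agrees.
- Chance of seeing at least one such failure: 1 − 0.95^60 = 0.954 with 60 men, and 1 − 0.95^72 = 0.975 with 72.

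The figure reproduces and is not in dispute.

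**4. What zero events would show under complete capture**

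- One-sided 95% upper bound, 72 men: 1 − 0.05^(1/72) = 4.1%.
- Two-sided 95% (exact) upper bound, 72 men: 1 − 0.025^(1/72) = 5.0%.
- One-sided 95% upper bound, 60 men: 1 − 0.05^(1/60) = 4.9%.

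**5. Illustration of incomplete capture (every s is an assumption)**

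Take an event with a true rate of 5% per man. Detection is 1 − (1 − 0.05s)^n. The upper bound after zero recorded events is the complete-capture bound divided by s.

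| Assumed s | Detection, n = 60 | Detection, n = 72 | Upper bound, n = 60 | Upper bound, n = 72 |
|---|---|---|---|---|
| 100% | 0.954 | 0.975 | 4.9% | 4.1% |
| 75% | 0.899 | 0.936 | 6.5% | 5.4% |
| 50% | 0.781 | 0.838 | 9.7% | 8.2% |
| 25% | 0.530 | 0.596 | 19.5% | 16.3% |

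The 95% detection property that the plan claims for process failures would carry over to adverse events only if capture were nearly complete.

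**6. The statement on excess risk**

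Excess risk is a difference from what would happen without the programme. The study has one arm, so even complete counts cannot estimate that difference. Section 4.4.3.1 itself reviews imaging for bone metastases, substitutes strength tests that would stress a lesion, and restricts exercises by metastatic site. These precautions suit an expectation of low risk better than an established absence of risk. The sentence enters neither calculation: 60 comes from step 3, and 72 from an allowance for attrition.

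**The case against.** The strongest reply is that Section 7.1 is a deliberate, resource-limited choice in a feasibility study whose primary endpoint is feasibility and acceptability, and that the men are seen often. Several parts of this stand.

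- **A reader might infer that events enter the record only if a man volunteers them.** Section 7.1 does not say only. It also has an investigator record any event from participation with significant negative consequences. A nurse is present to discuss symptoms in weeks 3, 5 and 11, nursing reviews are two-weekly (Section 4.3.2), and Section 5.0 schedules further nursing assessments. These contacts may prompt reports, although nothing in the protocol links them to adverse event recording.
- **A reader might infer that unrelated events are never recorded.** That is wrong from grade 3 upwards, where Section 7.1 applies no relatedness filter.
- **A reader might infer that skeletal complications are an endpoint, or that an adverse event rate decides whether the programme is rolled out.** Neither is in the documents. Skeletal complications are an item to record, and Section 2.1 makes roll-out depend on feasibility without naming a rate.
- **A reader might infer that the sample size rests on the absence of excess risk.** It does not; the sentence supports only the side argument about over-recruitment.
- **A reader might infer that the wider serious event scope is an error, or that a study pause is nearly certain.** Section 7.1 defines that scope expressly for this study, and any probability of a pause would need a grade 4 event rate that the documents do not give.

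What the reply does not answer is the mismatch itself. Scarce resources may explain 7.1, but 4.4.3.1 still promises a record that 7.1 does not deliver.

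**Conclusion.** The two sections contradict each other on which adverse events below grade 3 are recorded, and must be reconciled. If 7.1 governs, the frequency will tend to be understated. The direction follows from the text, while the size depends on a capture fraction that the documents do not give, so the 25% to 75% rows above are illustrations only. If 4.4.3.1 governs, the scope is complete but no method of eliciting events is stated.

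With complete capture, zero events in 72 men is compatible with a true per-man rate of up to 4.1% (one-sided 95%). The statement in Section 6.1 is therefore a premise that the study cannot confirm. No primary conclusion and no sample size figure changes. This should be fixed, but it does not invalidate the design.

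**What to change.** 1. Apply one recording scope in Sections 4.4.3.1 and 7.1, preferably the one that 4.4.3.1 already promises. Record first and judge relatedness afterwards.
2. Elicit events with one standard question at contacts that already take place, such as the supervised exercise sessions or the per-session collection of service use described in Section 4.4.4.
3. State the reporting window, and report per-man incidence with exact 95% confidence intervals.
4. If the narrower 7.1 scope is kept, amend 4.4.3.1 to match and label the reported frequency as passively ascertained and, below grade 3, essentially limited to potentially related events.
5. In Section 6.1, reword the statement on excess risk as an expectation. The 60 and 72 stay as they are.
6. The investigators should confirm that the adverse event scope (potentially related), the serious event scope (any cause) and the pause trigger are meant to differ. No pause rule is proposed here.

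The cost is protocol wording, one question at existing sessions, and the staff time to log, grade and assess more events. That time is a real burden, since Section 7.1 already cites resources. Option 4 avoids most of it, at the price of a less informative safety summary.
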